### Randomization and allocation concealment {16}

The randomization method employs variable block randomization with random-sized blocks. Professional statisticians not involved in data management utilize the Data Web data collection management system to generate a central random sequence, randomly allocating subjects in a 1:1 ratio and dividing them into two groups. Stratification is based on whether upper gastrointestinal endoscopic invasive treatment is planned, as this factor may influence the duration of the procedure and potentially affect the sedation success rate. Random numbers are placed in coded, opaque envelopes and entrusted to personnel not involved in anesthesia or data collection for management.

### Blinding

#### Who will be blinded {17a}

The intervention drugs in this study, propofol and remimazolam, have distinct properties and dosages, precluding the possibility of blinding the interventionist. However, the drug administration process will be concealed from the subject during drug injection, implementing a single-blind design in which only the patient is blinded. The study data collector remains mutually inaccessible. The outcome assessors in the study are the interventionists, who are not blinded to the study. However, the data analysis is conducted by individuals who did not participate in the intervention measures and are blinded to the participants’ identities.

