####  Primary outcome

The success rate of patients in both groups who successfully completed upper gastrointestinal endoscopy and treatment. Success will be evaluated using a composite endpoint index comprising the following criteria: (1) MOAA/S score of ≤ 3 points before endoscope insertion into the oral cavity, (2) no interruption of endoscopic examination due to inadequate sedation, (3) no occurrence of SpO_2_ < 90% during the examination, (4) no incidence of systolic blood pressure < 80 mmHg, systolic blood pressure ≥ 180 mmHg, heart rate (HR) ≤ 55 beats/minute, or *HR* > 100 beats/minute during the examination.

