### Sample-size calculation {14}

The study plans to enroll 576 patients. The basis for sample size calculation is as follows: According to the literature report [7], patients undergoing upper gastrointestinal endoscopy and treatment with propofol sedation had a completion rate without sedation-related complications of 79%. Using a two-sample *z*-test for proportions to assess the primary outcome measure, the estimated non-inferiority margin is an absolute difference of 10% for the primary outcome measure. Setting a non-inferiority difference value of 0.1, a power (1-β) of 0.8, and a one-sided α of 0.025, a total sample size of 522 cases is required for the calculation. Accounting for an anticipated loss to follow-up rate of 10%, the total sample size is 576 cases (288 participants per group).

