This study has limitations, including the single-blind methodology, which may introduce performance bias. However, outcome evaluators and statisticians will be blinded, and efforts will be made to adjust for bias. Additionally, the study is limited to participants from a single center, and the results may only be applicable to the Chinese population. The trial’s short duration (1-day treatment) focuses solely on the short-term sedative effect and safety impact of remimazolam.

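### The methods make the unblinded interventionists the outcome assessors, but the Discussion says outcome evaluators are blinded and relies on this to offset the single-blind design

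*Protocol article*

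**What the plan says.** Protocol article, Who will be blinded {17a}:

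- The drugs differ in properties and dosage, "precluding the possibility of blinding the interventionist".
- The injection is hidden from the patient, "implementing a single-blind design in which only the patient is blinded".
- On assessment: "The outcome assessors in the study are the interventionists, who are not blinded to the study".
- On analysis: "the data analysis is conducted by individuals who did not participate in the intervention measures and are blinded to" participants' identities.

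Protocol article, Discussion (limitations paragraph): single-blinding is conceded as a possible source of performance bias, followed by "However, outcome evaluators and statisticians will be blinded, and efforts will be made to adjust for bias".

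The Primary outcome section defines success by four components. The first is a MOAA/S score of at most 3 "points before endoscope insertion into the oral cavity". The second is "no interruption of endoscopic examination due to inadequate sedation". The third and fourth are the absence of SpO2, systolic pressure and heart rate values beyond fixed limits.

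**The concern.** The two sections answer the same question, whether those who assess outcomes know the arm, in opposite ways. The Discussion sentence also carries weight, because it is the reason given for not worrying much about the single-blind design. A reader judging risk of bias from the Discussion would credit the trial with masked outcome assessment. A reader of the methods would not.

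The primary endpoint is assessed during the procedure, so the conflict reaches it. MOAA/S is an observer's rating, and calling an interruption sedation-related is an attribution. Both can be influenced by knowing which drug was given. In a non-inferiority trial, any lean towards the new drug moves the estimate directly towards the claim that the trial is designed to test.

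**Working it through.** **1. Can the two statements be reconciled?**

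| Question | {17a} | Discussion |
|---|---|---|
| Who is blinded? | Among those taking part in the procedure, only the patient | Outcome evaluators and statisticians |
| Are outcome assessors blinded? | No; they are the interventionists | Yes |
| Are analysts blinded? | Yes, worded as to identities | Yes |

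The rows agree on analysts and conflict on assessors. Four other places might settle it:

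- Interventions {11a} says that an assessor must stay outside the examination and sedation plan. This closes the screening and consent text, before the sedation plan begins. It most naturally means the person assessing eligibility and taking consent.
- {17a} has a sentence on the study data collector being inaccessible. Its meaning is unclear, and the next sentence names the interventionists as assessors.
- Data management {19} gives data entry to staff uninvolved in the intervention. They work from a CRF that researchers have already filled in, so they cannot correct the original observation.
- Sensitivity analysis {20c} has a broadened success definition that keeps only the MOAA/S and interruption components. These are the two that depend most on judgement, so this analysis does not test robustness to unblinded assessment.

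None of these removes the conflict.

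**2. The plan's own design figure.**

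Inputs from Sample-size calculation {14}: control success 0.79, margin 0.10, one-sided alpha 0.025, power 0.80. The true difference is taken as 0, which is an assumption because the section does not state it.

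n per arm = (1.960 + 0.842)² × 2 × 0.79 × 0.21 / 0.10² = 260.4, rounded up to 261. The total is 522, as stated. The plan then enrols 288 per arm. The blinding point changes none of these figures.

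**3. What a shift in assessed success would do (illustration).**

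Place the truth exactly at the margin: propofol 79%, remimazolam 69%. Let assessment raise the recorded remimazolam rate by b, counted in percentage points of all remimazolam patients. With p = 0.69 + b and n = 288 per arm:

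- SE = √[0.79 × 0.21/288 + p(1 − p)/288]
- False non-inferiority rate = Φ(b/SE − 1.960)

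| b (points) | Patients of 288 | SE | b/SE − 1.960 | Rate, 288 per arm | Rate, 261 per arm |
|---|---|---|---|---|---|
| 0 | 0 | 0.0363 | −1.960 | 2.5% | 2.5% |
| 1 | 2.9 | 0.0361 | −1.683 | 4.6% | 4.5% |
| 2 | 5.8 | 0.0359 | −1.403 | 8.0% | 7.6% |
| 3 | 8.6 | 0.0357 | −1.120 | 13.1% | 12.3% |
| 5 | 14.4 | 0.0353 | −0.542 | 29.4% | 27.1% |

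Exact binomial enumeration with the same unpooled z-test agrees to within about 0.1 percentage point.

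**4. What the unit of b means.**

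At 69% success, failures are 31% of the arm. A shift of 3 points therefore means relabelling 3/31 = 9.7% of failures, and 5 points means 5/31 = 16.1%. Relabelling only 3% of failures is 0.03 × 31 = 0.93 points and gives 4.4%. Relabelling 5% of failures is 1.55 points and gives 6.3%.

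**The case against.** The best defence is that {17a} is the operative section, discloses unblinded assessment openly, and explains why the interventionist cannot be blinded. On that view the defect is one wrong sentence in the Discussion. This stands as a description of where the error sits. It does not make the error harmless, because the wrong sentence is the stated mitigation for the design's acknowledged weakness.

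Several stronger readings are tempting, and the documents do not support them:

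- **One person doses, scores and records everything.** {17a} speaks of interventionists in the plural and mentions a separate data collector. {11a} gives top-up decisions to the chief anesthesiologist and the choice of alternative sedation to the investigator. Intraoperative data collection does not say who rates MOAA/S or attributes an interruption.
- **The whole primary endpoint is subjective.** The SpO2, pressure and heart rate components are numeric limits, with SpO2 monitored continuously and blood pressure measured every 3 minutes. Data collection is on paper, but {19} does not say whether the original observation records are monitor output. These components are less exposed than the two judged ones.
- **Assessors favour remimazolam, and the error rate is 13% or 29%.** Nothing in the documents gives a direction or a size. A lean the other way would lower the false non-inferiority rate and cost power.
- **Analysts are not blinded.** Both sections affirm analyst blinding. Referring to identities and not to arm is loose wording, and arm coding is commonly left to the analysis plan, which is not shown.

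**Conclusion.** The contradiction is explicit and nothing in the protocol resolves it. On the operative methods text, outcome assessment is unblinded, and the assessor blinding used in the Discussion to offset the single-blind limitation does not exist. The bias risk falls mainly on the MOAA/S and interruption components.

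The size of the effect on the trial's conclusion cannot be derived. The calculation shows sensitivity only: at the margin, a shift of about 3 patients in 288 nearly doubles the 2.5% error rate, and about 9 patients takes it to 13.1%. It rests on assumed bias sizes, an assumed direction, true rates of 79% and 69%, 288 analysed per arm and an unpooled z-test.

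**What to change.** 1. Correct the Discussion so that it agrees with {17a}: outcome assessment is unblinded, and detection bias in the primary endpoint is a limitation alongside performance bias. This costs only wording.

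2. Where monitor records are stored or printed, have the data-entry staff described in {19} as uninvolved in the intervention take SpO2, systolic pressure and heart rate from those records with arm hidden.

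3. Pre-state a sensitivity analysis on those monitor-derived components alone. It complements the one in {20c}, which keeps only the two judged components.

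Steps 2 and 3 need a small transcription effort by existing staff. Their limit is availability: Trial status {3} says that enrolment began in December 2022 and was in progress, and the documents do not say whether monitor records were kept. For patients already treated they may not exist, and the report should then state how many patients the sensitivity analysis covers. The text correction in step 1 does not depend on this.

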### Interventions {11a}

Upon obtaining signed informed consent from the subject, the following process is executed (Figs. 2 and 3):Screening periodAfter the patient enters the endoscopy examination room and decides to undergo upper gastrointestinal endoscopy treatment, the researcher collects information on the patient’s demographics, medical condition, and proposed examination plan. An independent anesthesiologist evaluates the patient’s examination plan before randomization, and eligible patients are selected based on the inclusion/exclusion criteria. Patients should be assessed by researchers who are knowledgeable about the protocol and authorized to do so in a quiet environment. The study’s purpose, methods, potential benefits, and risks must be thoroughly explained to the patient and/or their representative, and data collection and follow-up procedures before, during, and after the examination must be detailed.The researchers should address the patient and their family members’ questions in detail, allowing sufficient time for consideration and obtaining informed consent from the patient and/or their representative on a completely voluntary basis. The assessor must not be involved in the patient’s examination, sedation, or anesthesia management plan. *Sedation management plan*: An anesthetist with the title of attending physician or above will implement the sedation and anesthesia plan. The patient enters the endoscopy consultation room’s preparation area and takes 10 g of lidocaine gel (containing 0.2 g of lidocaine) orally 5 min before the examination. The patient assumes a left lateral position on the treatment bed in the endoscopy consultation room, and basic vital signs including noninvasive blood pressure (NIBP) of the right upper arm, electrocardiogram, and pulse oxygen saturation (SpO_2_) are monitored. Oxygen is continuously administered through a 4L/min nasal cannula throughout the procedure until the patient fully awakens. A venous line is established, and sufentanil 5 μg is administered intravenously. Patients scheduled for upper gastrointestinal endoscopy are randomized to receive one of two sedative drug infusions: propofol in group C or remimazolam in group R. In group C, patients receive a single dose of propofol at 1.5 mg/kg, while in group R, patients receive a single dose of remimazolam at 0.15 mg/kg, both administered within 1 min. According to the domestic expert consensus, moderate or deep sedation is required for upper gastrointestinal endoscopic examination. Therefore, the MOAA/S score (Appendix 2) should be assessed 1 min after propofol injection. If the MOAA/S score is greater than 3 points, propofol 0.5 mg/kg or remimazolam 0.05 mg/kg should be administered repeatedly until the MOAA/S score is less than or equal to 3 points, with a maximum of five repetitions. The VAS (Appendix 3) should be assessed during propofol or remimazolam injection.*Intraoperative monitoring*: Intraoperative monitoring includes electrocardiogram, noninvasive blood pressure, pulse oxygen saturation, and, when necessary, body temperature, urine output, end-tidal carbon dioxide concentration, and blood glucose levels.*Sedation maintenance plan*: During the examination procedure, the chief anesthesiologist determines whether to administer additional trial medication based on the surgical process and duration. Propofol (0.5 mg/kg) or remimazolam (0.05 mg/kg) is administered in single doses with a minimum interval of 1 min to maintain the patient at an appropriate level of sedation (MOAA/S score ≤ 3). If sedatives are insufficient to maintain appropriate sedation during the examination, the investigator may decide to use alternative sedative agents (midazolam).*Examination plan*: Based on the type of lesion, the endoscopic examination of the upper digestive tract in our hospital may include, but is not limited to, upper gastrointestinal inflammation, tumors, ulcers, polyps, gastroesophageal varices, and gastrointestinal strictures. According to the type of endoscopic treatment of the upper gastrointestinal tract, it may include, but is not limited to, sclerotherapy, argon plasma coagulation, high-frequency electrocautery, and submucosal dissection. Various procedures are conducted following established clinical surgical protocols. *Postoperative management plan*: After the examination or procedure, the patient enters the anesthesia recovery room, where continuous monitoring of ECG, noninvasive blood pressure, and oxygen saturation occurs. The MOAA/S score is assessed every 5 min. Once the score reaches 5 points for three consecutive assessments, and blood pressure, heart rate, and oxygen saturation are normal and stable, the patient can leave the recovery room accompanied by a companion. In case of special circumstances, refer to the adverse event handling procedures.

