#### Secondary outcomes

*Sedation efficacy outcomes*: (1) MOAA/S score after single administration; (2) time required to achieve a MOAA/S score of ≤ 3 points following single administration; (3) for patients not achieving adequate sedation depth after a single dose and documentation of additional medication doses and frequency; (4) total amount and number of additional administrations of remimazolam or propofol in both groups during the entire course of upper gastrointestinal endoscopy and treatment; (5) duration from the initiation of medication injection to the completion of upper gastrointestinal endoscopy and treatment; (6) type, frequency, and dose of alternative or additional remedial drugs required when the upper limit of supplementary dosage is exceeded; and (7) operator satisfaction.

*Consciousness recovery outcomes*: (1) Time to full awakening; (2) use of sedative antagonist flumazenil, if applicable; (3) assessment of patients’ recall of upper gastrointestinal endoscopy and treatment process using the Brice questionnaire (Appendix 4) after awakening; (4) duration of patients’ recovery; and (5) overall patient satisfaction.

*Safety outcomes*: (1) Incidence of hypertension or hypotension during the procedure and in the recovery room, (2) incidence of tachycardia or bradycardia during the procedure and in the recovery room, (3) incidence of low oxygen saturation during the procedure and in the recovery room, (4) airway intervention rate during the procedure and in the recovery room, (5) incidence of coughing within 1 min after endoscope insertion, (6) incidence of coughing during upper gastrointestinal endoscopy and treatment, and (7) incidence of injection-related pain.

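### The Discussion counts the statisticians as blinded, but the blinding section keeps only patients' identities, not the treatment arm, from the analysts

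*Protocol article*

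**What the plan says.** Who will be blinded {17a} describes the trial as "implementing a single-blind design in which only the patient is blinded". On assessment it says: "The outcome assessors in the study are the interventionists, who are not blinded to the study". On analysis it says that the work is "conducted by individuals who did not participate in the intervention measures and are blinded to the participants’ identities". It does not mention the treatment group in connection with the analysts.

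The limitations paragraph of the Discussion concedes that the single-blind design may bring performance bias, and then answers: "However, outcome evaluators and statisticians will be blinded, and efforts will be made to adjust for bias".

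Dose is both recorded and analysed. Intraoperative data collection calls for the trial-drug dose at the time of insertion, and Secondary outcomes include the "total amount and number of additional administrations of remimazolam or propofol in both groups".

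**The concern.** The Discussion relies on a safeguard that the methods do not set up. An analyst who does not know a patient's name may still know which drug the patient received.

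This matters because few other protections remain. The interventionists know the drug and also assess the outcomes. There is no data monitoring committee (section {21a}) and no audit plan (section {23}). In a non-inferiority trial, decisions on who is left out and how missing outcomes are treated can shift the estimate against the 10% margin. Such decisions are best made without sight of the arm.

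**Working it through.** **1. The plan's own figure.** Sample-size calculation {14} gives 79% success, a margin of 0.10, one-sided alpha 0.025 and power 0.80. Per arm: (1.960 + 0.842)² × 2 × 0.79 × 0.21 / 0.10² = 260.4, so 261, or 522 in total, as stated. Nothing below changes this figure.

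**2. The two statements side by side.**

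| Role | Who will be blinded {17a} | Discussion, limitations |
|---|---|---|
| Patient | Blinded, and the only one so described | Design called single-blind |
| Outcome assessors | The interventionists; not blinded | Blinded |
| Analysts | Separate from the intervention; not told who the participants are | Blinded |

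The second and third rows do not agree across the columns. No section says that arms are coded for analysis. The labels in Interventions {11a} are group C for propofol and group R for remimazolam.

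**3. Could identities mean group identity?** Confidentiality {27} describes a unique code that anonymises personal details, which is the ordinary sense of hiding identity. Where the article means allocation, as in the unblinding section {17b}, it speaks of the intervention received or assigned. Section {17a} uses no such term for the analysts, so the group-identity reading is possible but unlikely.

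**4. Would dose reveal the arm?** Interventions {11a} states for the first dose: "patients receive a single dose of propofol at 1.5 mg/kg, while in group R, patients receive a single dose of remimazolam at 0.15 mg/kg". For repeats it states "propofol 0.5 mg/kg or remimazolam 0.05 mg/kg should be administered repeatedly until the MOAA/S score is less than or equal to 3 points", with at most five repetitions.

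- Largest remimazolam induction total: 0.15 + 5 × 0.05 = 0.40 mg/kg.
- Smallest propofol induction total: 1.5 mg/kg.
- Ratio: 1.5 / 0.40 = 3.75. Induction totals in raw mg could overlap only if a remimazolam patient weighed at least 3.75 times as much as a propofol patient.
- Remimazolam top-ups needed to reach the propofol starting dose: (1.5 − 0.15) / 0.05 = 27.

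The 0.40 mg/kg ceiling covers induction only, because no cap on maintenance doses is stated. Whole-course totals are still separable when the number of top-ups, k, is known: (1.5 + 0.5k) / (0.15 + 0.05k) = 10 for every k. With weight and count to hand, the arm is evident for any patient dosed as stated.

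**5. Which choices does the text leave open?**

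- Withdrawal criteria drop outcomes for six reasons, among them the investigator's judgement and unrecorded data. Efficacy evaluation {20a} uses an ITT population of everyone randomised. How the two are reconciled is undecided.
- Sensitivity analysis {20c} includes a per-protocol set, and mentions both missing-data indicators and multiple imputation.
- Efficacy evaluation {20a} lists a chi-square test and both unadjusted and adjusted risk differences. It does not say which risk difference is set against the margin.
- The covariates are listed, but their coding is not given.

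**The case against.** Several points on the other side are sound.

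- **Analysts' access to dose is not documented.** A reader might infer that the analysis file exposes every arm. The article says only that dose is recorded and is a secondary outcome. It does not describe the export or when fields are released. Such detail commonly sits in an analysis plan or data-management plan that is not shown, so its absence is no finding. The dose argument therefore stands only as a conditional.
- **The primary analysis is not wide open.** A reader might infer that the primary analysis as a whole could be chosen knowing the allocation. Efficacy evaluation {20a} names the ITT population, the test, the risk-difference model and the covariates, and the vital-sign thresholds in the composite are numeric. Per-protocol is a sensitivity analysis and subgroups are exploratory. The withdrawal decisions are not assigned to the analyst.
- **Masking would not cure the conflict between the exclusions and ITT.** That conflict is a separate defect. Masking would only ensure that it is resolved without sight of the arm.
- **Two further suspicions lack support.** Flumazenil use does not prove the arm, because midazolam may be given as alternative sedation without restriction to one group. Nothing says that the statistician who generated the sequence also runs the analysis.
- **The outcome-evaluator half of the Discussion sentence is the plainer error.** This is fair: it bears on the observer-rated parts of the composite, the MOAA/S score and interruption for inadequate sedation. It adds to the point about analysts and does not displace it.

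None of this removes the disagreement between {17a} and the Discussion. A fuller document could settle which statement is right, but could not make both true as printed.

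**Conclusion.** The point holds in limited form. As written, the methods do not provide the masking of statisticians that the Discussion claims, and the same Discussion sentence is contradicted outright on outcome evaluators.

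The documents do not show that analysts will know the allocation. They show that allocation masking is asserted in one place and not set up in the place that governs it. The dose separation rests on two assumptions: that the fields reach the analyst unmasked, and that patients are dosed as stated. Exposure is confined to the choices listed above, and it would shrink further if an unseen analysis plan locks them before the data are seen.

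No design figure changes and no bias can be computed from the documents. The correction is worth making because it is cheap and the article relies on the safeguard.

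**What to change.** In Who will be blinded {17a}, say that analysts are masked to treatment allocation, with arms coded A/B in place of C/R. Hold drug name and dose fields in a separate file, released only after the analysis populations, the missing-data decisions and the primary result on coded arms are locked. If this will not be done, delete the word statisticians from the Discussion sentence.

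In either case, correct that sentence on outcome evaluators so that it agrees with {17a}.

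As optional precautions, flumazenil use can go in the withheld file, and the statistician who generated the sequence can be kept off the primary analysis.

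The cost is a paragraph of text and a split data export, with dose outcomes analysed in a second step. Patient care and sample size are unaffected.
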